#### Depression

The Patient Health Questionnaire-8 (PHQ-8; [41]) is an 8-item measure of depression severity based on 8 of the 9 item criteria of the DSM-IV. The measure was derived from the PHQ-9 however; the ninth question was omitted from this study because of ethics reasons around asking about suicidality. Depression severity is scored based on the presence of depressive symptomology in the previous 2 weeks of measure admission. The scale uses a 1 (not at all) to 4 (nearly every day) ordinal scale with higher scores indicating higher levels of depressive symptomology. The PHQ-9 has been shown to have good criterion and construct validity and excellent internal consistency [42]. The PHQ-8 shares similar properties in terms of validity and reliability and is therefore an adequate alternative to its 9-item scale counterpart [41].

#### Social anxiety

The Mini-Social Phobia Inventory (Mini-SPIN; [43]) is a brief 3-item measure of generalised social anxiety disorder. The measure employs a 5-point ordinal scale form 1 (not at all) to 5 (extremely), with higher scores indicating a greater level of generalised social anxiety. The Mini-SPIN has shown high sensitivity in detecting social anxiety disorder [43].

#### Quality of life

The European Health Interview Survey-Quality of Life – 8-Item Index (EUROHIS-QOL-8; [44]) is an 8-item measure of quality of life consisting of questions that assess overall QOL, general health, energy, daily living activity, self-esteem, social relationships, finances, and home. The measure is derived from the WHOQOL-BREF and shares a similar 5-point Likert-scale response format. The scale has demonstrated good qualities in term of internal consistency (Cronbach’s alpha = 0.83) and satisfactory convergent and discriminant validity [44].

#### Positive affect

The Positive and Negative Affect Schedule – SF (PANAS-PA 10 item; [45]). is a 10-item positive affect subscale measure of the PANAS scale. The measure asks participants to rate the extent to which they feel a particular emotion along a 5-point Likert scale ranging from 1 (very slightly) to 5 (extremely). This subscale measure has been shown to have high levels of internal consistency [45] and acceptable levels of convergent validity [46].

#### Stress

The Perceived Stress Scale-4 (PSS-4; [47]) is a four-item measure of stress was derived from the original 14-item Perceived Stress Scale (PSS). This measure consists of both positively and negatively worded items that asses an individual’s evaluation of stressful events. The measure employs a 5-point ordinal scale ranging from 0 (never) to 4 (very often). The PSS-4 has been shown to negatively correlate with levels of perceived health, social support, being male, and older age [48]. The scale has demonstrated fair reliability and adequate psychometric properties [48].

### Implementation secondary outcomes

#### Feasibility

Feasibility will be the following: having a high retention rate (i.e., < 40% drop-out).

#### Acceptability

We measure acceptability around these factors, including how connected (1 not at all connected to 10 very connected), how meaningful was the KIND Challenge activity (1 not very meaningful to 10 very meaningful), how safe they felt when completing the KIND Challenge (1 not very safe to 10 very safe), how positive they felt (1 not very positive to 10 very positive), how comfortable they felt doing the KIND Challenge activity (1 not at all comfortable to 10 very comfortable). It is anticipated that the Nextdoor KIND Challenge will yield ratings of more than 5 indicating higher levels of acceptability across these outcomes. These questions were specifically developed for the study (see Supplementary Table 1 section c).

#### Safety

We assess for unintended harms (e.g., conflict) during this period. In this case, we measure the occurrence of neighbor conflict because of the KIND Challenge. It is anticipated that the KIND Challenge activity is safe for participants with no unintended conflicts reported. This question was developed for the study (see Supplementary Table 1 section d).

#### Post-KIND challenge activity

*Post intervention,* participants will be asked if they completed either their nominated KIND Challenge activity or any KIND Challenge activity over the past month. Type of support can be categorized based on participant selection. Participants can also select “other” activities that were not listed. If the “other” box activity is selected, participants are asked to describe the activity in detail via a free text entry box. Responses in the free text box entry will be coded independently by two research assistants not related to this trial. Inter-rater reliability between coders will be calculated to ensure adequate reliability of categorization. For each activity, participants will be asked how frequently they completed the activity (1 = once to 4 = more than 5 times), the duration of the activity (1 = less than 10 min to 5 = more than 2 h), how connected to others they felt after completing the selected activity (1 = not at all connected to 10 = very connected). They can select more than one activity and will rate each activity according to those scales. If participants have not completed a KIND Challenge activity, an additional multiple-choice question will be included to assess for what reasons the activity could not be completed (e.g., lack of time, that they forgot, illness, work, stress etc). Participants were then asked to reflect on the KIND Challenge overall including how meaningful and safe they found the challenge, how positive they felt after the challenge, and how connected and comfortable they felt towards their neighbours because of the challenge. These questions were specifically developed for the study (see Supplementary Table 1 - section c).

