**Methods:**

This study is made up of three randomised controlled trials conducted in three countries. Each randomised controlled trial has two arms (intervention vs waitlist control) and is designed to compare the effectiveness of the KIND challenge, which involves doing at least one act of kindness per week within a four-week period. This study will recruit users of an online community, be randomised online, and will be conducted using online assessments. We will first explore the effects of the intervention on the primary outcome of loneliness, followed by secondary outcomes, social isolation, neighbour relationship quality and contact, mental health symptoms, stress, quality of life, and positive affect. Further, we will assess the feasibility, acceptability, and safety of the KIND Challenge.

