### Objectives

The overall objective is to examine the social and psychological impact of kindness on a community sample. This will be examined by asking community members within an online social networking platform, Nextdoor, to participate in performing at least four acts of kindness over a four-week period. We refer to this as the Kindness Is Nextdoor (KIND) challenge.

The primary intervention objective of the Nextdoor KIND Challenge is to reduce loneliness in the Nextdoor online communities across three countries (Australia, United States, United Kingdom). We expect significant changes to loneliness. Specifically, it is anticipated that challenge participants will show significantly greater improvement in loneliness compared with the control group, after accounting for known covariates.

A secondary intervention objective of the Nextdoor KIND Challenge is to reduce social isolation risk in the Nextdoor online communities across three countries (Australia, United States, United Kingdom). It is anticipated that challenge participants will show significantly greater reduction in social isolation when compared with the control group.

An additional secondary intervention objective of the KIND Challenge is to improve neighbourhood relationship quality and contact, and we expect significant improvements in neighbourhood ties both in terms of relationship quality and contact. It is anticipated that KIND Challenge participants, compared with the control group, will show greater improvement in neighbourhood relationship quality as measured by social cohesion and trust, perception that their neighbourhood is improving, higher importance around getting to know their neighbours, greater positivity and lower negativity towards their neighbors, and lower neighbourhood conflict. It is anticipated that KIND Challenge participants compared with the control group will also report significantly more neighbourhood contacts compared with the control group.

There are further secondary objectives of the KIND Challenge to improve mental health outcomes, that is lower depression, social anxiety, and stress levels, improve quality of life, and increase positive affect, with those participants in the KIND challenge showing greater positive effects when compared with control participants.

We also anticipate that acts of kindness will be feasible, acceptable, and safe to do for community participants (see apriori in Implementation secondary outcomes section).

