The third objective of this intervention is to examine factors that may moderate the effects, including dosage, pre-existing levels of social connection, type of kindness activity, and adherence. Interventions are rarely adhered to in full, and variability in compliance and engagement is commonplace; moreover, this variability is associated with differences in expected outcomes. It is therefore important to take measures of engagement with the intervention to explore how variability in engagement moderate outcomes. First, it is anticipated that the level of adherence (do participants complete the instructed four acts of kindness) and engagement, or *dosage*, in terms of frequency and duration of KIND activity will make a difference to loneliness and social isolation severity. Second, the more connected participants feel in relation to the KIND activity will impact outcomes and participants are likely to feel less lonely. Third, it is recognized that some acts of kindness may have greater effect than others, and specifically how do different acts of kindness that provide either emotional, tangible, informational, belonging, or companionship support impact on loneliness and social isolation will be examined. Therefore, both quantity and quality of engagement with the KIND challenge can be modelled as predictors of primary outcomes of loneliness and social isolation. Finally, understanding engagement and adherence to the intervention is fundamental to exploring the feasibility and making recommendations for future interventions. Therefore, an additional purpose of the study is to identify reasons, (i.e., lack of time, illness, work, stress etc.) for lack of engagement and adherence to the KIND challenge. In terms of analysis, traditional approaches to dealing with (non) compliance in RCTs (e.g., ‘as treated’) produce biased estimates, so we will use Complier Average Causal Effect (CACE) estimation to explore the impact of compliance to implementing the intervention. CACE allows exploration of treatment effects where there is less than ideal levels of participant compliance (as opposed to the offer of said intervention, as in ITT used for H1 above).

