## Methods

### Trial design

This study is made up of three RCTs and each RCT has two conditions: the KIND Challenge condition and a waitlist control condition. A person enrolled into the KIND Challenge condition will be asked to do acts of kindness at least four times for a duration of 4 weeks and will complete three online assessments. A person enrolled into a waitlist control condition will wait 4 weeks before starting the KIND Challenge and will be required to complete four online assessments. The evaluation of the KIND Challenge will be pre-registered prior to the study launch. Please refer to Fig. 1.

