### Adherence and engagement variability

Variability in adherence and engagement will be measured in the participants allocated to the KIND Challenge group. First, adherence can be measured by the frequency and duration of KIND acts completed during the 4-week intervention. Second, an index of level of engagement for each type of activity completed (i) emotional support, (ii) tangible support, (iii) informational support, and (iv) belonging support, (v) companionship support can be created by combining the frequency and duration to produce an indicator of dosage for each type of KIND act. Third, the impact of overall engagement with the KIND Challenge can be modelled via meaningfulness, degree of positive feelings and sense of connectedness to others.

Linear multiple regression modelling in Mplus 8.3, will be employed to model the adherence and engagement as predictors of post 4-week intervention outcomes (H7), across the primary outcome of loneliness, and secondary outcome of social isolation, a neighbourhood relationship quality and contact, neighbourhood connectedness, and mental health. As with the H1–4 the model building approach will be used.

Reasons for non-compliance will also be captured and explored to assess barriers and challenges to competing the KIND activity, as measured by frequencies of lack of time, forgot, illness, work stress, family pressures or other.

CACE estimation will be employed using Mplus 8.3 to examine whether the effects noted in ITT analyses (H1–4) change once intervention compliance is taken into account. Participant demographics and baseline outcome variables will be used as predictors of the latent class compliance variable. Compliance will be assessed via dosage (i.e., number of kind acts completed; compliers vs. non-compliers). The CACE analysis will follow the same regression model building approaches detailed in H1–4.

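### The banded frequency item leaves some answers unclassifiable around four acts, and the instruction to participants is worded in two ways that are not equivalent

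*Protocol article*

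**What the plan says.** **Instruction.** The Abstract (Methods) describes the challenge as "doing at least one act of kindness per week within a four-week period". Objectives describes it as "performing at least four acts of kindness over a four-week period", and Trial design says that a person in the challenge arm "will be asked to do acts of kindness at least four times for a duration of 4 weeks". The intervention section adds a weekly reminder e-mail but describes no weekly record of acts.

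**Adherence and compliance.** The third objective, under Objectives, explains adherence by asking "do participants complete the instructed four acts of kindness". Adherence and engagement variability then measures adherence by frequency and duration. For the CACE analysis it states: "Compliance will be assessed via dosage (i.e., number of kind acts completed; compliers vs. non-compliers"). H8 likewise refers to the number of acts. Neither place gives a cut-off.

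**Measurement.** Under Post-KIND challenge activity, participants report on the past month in one survey. They may select several activities and are asked, for each, "how frequently they completed the activity (1 = once to 4 = more than 5 times"). The limits of codes 2 and 3 are not printed; the article refers to Supplementary Table 1, which is not shown. The one-month follow-up survey uses the same scale.

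**The concern.** The adherence criterion and the complier variable are both stated as numbers of acts, but the survey collects a number only in bands, separately for each activity type. A total therefore has to be built by adding bands, and some totals will span both three and four. If four is the line, those participants fall on either side of it by convention.

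CACE depends directly on who is called a complier, so the scoring convention feeds into the H8 estimate. The open top code also limits the dosage index that combines frequency and duration for H7. In addition, a person who does four acts in one week meets the wording in Objectives and Trial design but not that in the Abstract, and the item cannot show which pattern of timing occurred.

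**Working it through.** There is no stated figure to reproduce on this point. The check enumerates what the item can and cannot distinguish.

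**Inputs**
- Line tested: at least four acts (Objectives; Trial design).
- Code 1 is exactly 1 act; code 4 is 6 or more (Post-KIND challenge activity).
- Codes 2 and 3 must cover 2, 3, 4 and 5. Assumption: contiguous bands without gaps, which allows three splits.
- One to six activities per person (five support types plus the free-text option). Assumption: each act is reported under one type only.

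**Rule.** For a set of codes, let L be the sum of the lower limits and U the sum of the upper limits. The total is surely at least four if L ≥ 4 and surely under four if U ≤ 3. It is undecidable if L ≤ 3 and U ≥ 4.

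| Bands for codes 2 and 3 | One activity (4 patterns) | Two activities (10 patterns) | Three to six activities |
|---|---|---|---|
| 2 and 3–5 | code 3: L = 3, U = 5, undecidable | none | none |
| 2–3 and 4–5 | none | once plus code 2: L = 1 + 2 = 3, U = 1 + 3 = 4, undecidable | none |
| 2–4 and 5 | code 2: L = 2, U = 4, undecidable | once plus code 2: L = 1 + 2 = 3, U = 1 + 4 = 5, undecidable | none |

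So the splits leave 1, 1 and 2 undecidable patterns respectively. With three activities, three answers of once total exactly 3, and any other combination has L of at least 1 + 1 + 2 = 4. With four or more activities, L is at least 4. Hence nothing is undecidable from three activities upward.

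**Top of the scale.** Six acts and thirty acts of one type both receive code 4.

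**The two instructions.** One act in each of four weeks gives at least 4 × 1 = 4 acts, so the weekly wording implies the total wording. The reverse fails: four acts in one week give a total of four with three weeks empty. Within one activity type, both histories give the same code under any banding.

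**Why classification matters for H8.** If assignment has no effect in non-compliers, CACE ≈ ITT effect ÷ complier share. As an illustration, take the article's minimum detectable effect of .14 as the ITT effect, with assumed complier shares of 60% and 40%: .14 ÷ .60 = .23 and .14 ÷ .40 = .35. These shares only show the direction and sensitivity. The documents give no basis for estimating how many participants would be reclassified.

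**The case against.** - **Few patterns are affected, and the labels are unseen.** For at least four acts, most answers are decided. With bands 2–3 and 4–5, every single-activity answer is. This stands and limits the point. However, all three contiguous splits leave something undecided, so seeing the supplement would show which patterns are affected but would not remove them.
- **No complier cut-off of four is stated.** A reader might infer that compliance turns on four acts. The documents tie four to adherence only; for compliance it is an inference. A split into any act versus none would be fully measured, because participants are asked whether they completed any activity. The cut-off may also properly sit in an analysis plan that is not shown. All of this stands. But such a plan can choose a cut-off; it cannot recover counts that the item did not collect.
- **H7 uses graded predictors.** Frequency and duration enter a regression, and an ordinal code can serve there. This largely stands; what remains is the loss of information above five acts.
- **No analysis defines adherence by week.** The weekly wording is in the Abstract, and the weekly element of the intervention section is a reminder. This stands: the missing timing is a measurement gap only if the reconciled instruction turns out to be weekly.
- **Timing.** Trial status gives dates of July 2020 to January 2021, so changing the survey may no longer be possible. The fix allows for this.

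**Conclusion.** The point holds in a limited form. Under any contiguous banding, one or two answer patterns cannot be placed below four or at four and above, and counts above five within a type cannot be told apart. The two wordings of the instruction are not equivalent and must be reconciled; this review does not say which is right. The consequences reach the H8 CACE analysis and the adherence part of H7. The primary ITT comparison (H1) does not use complier status and is untouched.

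Two further readings are not supported. One is that the item cannot tell in general who did four acts: it can for most patterns and, on the stated assumptions, for everyone reporting three or more activities. The other is that participants close to four acts are generally misclassified: under bands 2–3 and 4–5, someone who did four acts of a single type is classed correctly, and the share affected is unknown.

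The result rests on contiguous bands and on each act being reported under one type. If one act is reported under several types, the summed total over-counts, and the finding for three or more activities no longer holds. Overall this is an inexpensive improvement to secondary analyses.

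**What to change.** 1. Reconcile the Abstract, Objectives and Trial design into one stated instruction.
2. At post-intervention, replace the frequency code with a whole-number count of acts per activity type. Do the same at the one-month follow-up so that the H6 comparison stays on one format. Use the counts in the dosage index.
3. Add an item on the number of weeks with at least one act only if the reconciled instruction is weekly.
4. Define compliers from the total count against the reconciled instruction.

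The cost is one changed response format and at most one added question, with slightly more recall effort and some rounding in the reported counts.

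If data collection has closed, state before analysis how banded answers are summed across activities. Report H8 with the ambiguous patterns classed first as compliers and then as non-compliers, and say plainly that weekly completion was not measured. That costs a short statement and one repeated analysis.

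### The structured question on reasons for not completing is triggered by doing no activity, not by doing fewer than the instructed four acts, so the reported reasons for non-compliance would omit partial adherers

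*Protocol article*

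**What the plan says.** **Instruction and adherence.** The Trial design section states that a participant in the KIND Challenge arm "will be asked to do acts of kindness at least four times for a duration of 4 weeks". The Objectives expect outcomes to depend on "the level of adherence (do participants complete the instructed four acts of kindness) and engagement". The same section makes it a further purpose of the study to identify reasons "for lack of engagement and adherence to the KIND challenge".

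**Collection.** Under Post-KIND challenge activity, "participants will be asked if they completed either their nominated KIND Challenge activity or any KIND Challenge activity over the past month". The section then says: "If participants have not completed a KIND Challenge activity, an additional multiple-choice question will be included to assess for what reasons". Examples of such reasons are time, forgetting, illness and work. Those who did complete something rate each activity for frequency, duration and connectedness.

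**Analysis.** The Adherence and engagement variability section says: "Reasons for non-compliance will also be captured and explored to assess barriers and challenges to competing the KIND activity". The results are to be reported as frequencies of much the same list of reasons. The same section says of the CACE analysis: "Compliance will be assessed via dosage (i.e., number of kind acts completed; compliers vs. non-compliers". It gives no cut-point.

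**The concern.** The trigger for the reasons question and the standard it is meant to explain are set at different levels. The standard is four acts and the trigger is none. Someone who did one act and then stopped has not followed the instruction, but on the stated routing is not asked why.

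The protocol expects such people. The Objectives say that full adherence is rare and that variation in compliance is common, and H7 and H8 are built on graded engagement and dose. The Objectives also treat understanding of adherence as basic to judging feasibility and to recommendations for later interventions.

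What is at stake is the meaning of one descriptive table. Frequencies headed as reasons for non-compliance would be read as covering everyone who fell short, when they would cover only those who completed no activity. The reasons for never starting and for stopping short may differ. This is a gap in data collection, so no later analysis can fill it.

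**Working it through.** The plan states no figure on this point that could be reproduced. The check sets the sections side by side.

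**1. Standard.** The Objectives and Trial design both give four acts over four weeks. The Abstract's minimum of one act a week for four weeks comes to the same number: 1 × 4 = 4.

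**2. Trigger.** The lead question asks about the nominated activity or any activity. The reasons question follows when an activity has not been completed. No threshold of four appears in that section.

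**3. Routing that results.**

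| Acts done | Meets the instructed four? | Shown the structured reasons question? |
|---|---|---|
| 0 | No | Yes |
| 1 to 3 | No | No |
| 4 or more | Yes | No |

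**4. Source of the planned frequencies.** The reasons listed in the analysis section (time, forgetting, illness, work stress and others) largely match those of the routed question, so that question appears to be the planned source.

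**5. Other items that might fill the middle row.** The Post-kind challenge overall impact section has open-ended items, with no completion filter stated, on obstacles to connecting and on how the Challenge was run. The Follow up KIND challenge activity section asks those who did not continue for their main reasons in free text. The first concerns connecting, not completing the acts. The second concerns the follow-up month. The analysis section names neither as a source.

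**6. Size.** Among post-intervention respondents below four acts, the share not asked is

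share = p(1–3) / [p(0) + p(1–3)].

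The protocol gives neither proportion. Assumed splits show only how the formula behaves:

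- p(0) = 10%, p(1–3) = 30%: 30/(10 + 30) = 75%
- p(0) = 20%, p(1–3) = 20%: 20/(20 + 20) = 50%
- p(0) = 30%, p(1–3) = 10%: 10/(30 + 10) = 25%

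These results restate the assumptions and are not estimates for this trial.

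**7. Can existing items identify those below four?** Not reliably. Frequency is recorded per activity in four bands, from once (band 1) to more than five times (band 4). If there are no gaps, bands 2 and 3 share the counts 2 to 5. The article does not give the division, and each possible one leaves some cases undecided:

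- {2} and {3, 4, 5}: band 3 alone straddles four.
- {2, 3} and {4, 5}: one activity in band 1 plus another in band 2 totals 1 + 2 = 3 or 1 + 3 = 4.
- {2, 3, 4} and {5}: band 2 alone straddles four.

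Routing on fewer than four acts therefore needs a question about the total.

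**The case against.** The strongest reply is that the branch itself is not visible. The article summarises an instrument whose items are in Supplementary Table 1, which is not shown, and its wording is loose. Participants nominate activities in advance, so not completing an activity could mean not completing the nominated one, and the question might then reach some partial adherers. This stands as a caution. A reader might infer as settled fact that only people with no acts at all are asked. The text supports that as the natural reading, since the lead question accepts any activity, but not as a certainty.

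A reader might also infer that the barriers of partial adherers are never recorded. The documents do not support that either. The open-ended items after the Challenge and at one month may capture some of them. What is missing is a planned, structured reason for falling short of four acts.

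It can further be said that four acts is a parenthetical remark in the Objectives, and that the analysis section measures adherence by frequency and duration and sets no cut-point for compliers. This is correct about CACE. The four-act standard rests on the Objectives and Trial design, where it is the instruction given to participants.

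Finally, the output is descriptive. It does not enter the loneliness comparison, the ITT or CACE estimates, or the stated criteria for feasibility, acceptability and safety. That stands, and it limits the weight of the point.

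**Conclusion.** The point holds in a limited form. On its natural reading, the protocol shows the structured reasons question only to participants who completed no KIND activity. It sets the instruction at four acts and promises reasons for lack of adherence and for non-compliance. Followed as written, the plan gives barrier frequencies that leave out participants who did one to three acts.

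The number affected is not given, and nothing in the protocol allows it to be estimated. The conclusion assumes that not completing an activity means completing none, and that the routed question is the source of the planned frequencies. If the survey routes differently, the text of the Post-KIND challenge activity section still needs to be reconciled with the Objectives and the analysis section.

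This is a minor issue, confined to a descriptive implementation result.

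**What to change.** If the survey can still be changed:

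- Add one post-intervention item asking whether at least four acts were completed in total, because the banded frequencies may not show this.
- Show the existing multiple-choice reasons question to everyone below four.
- In the Adherence and engagement variability section, state that reasons will be tabulated separately for those who did none and those who did one to three.

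The Trial status section gives a period ending 31st January 2021. If data collection is over, label the frequencies, in the analysis section and in the report, as reasons for completing no activity and not as reasons for non-compliance in general.

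The cost is one or two extra short items for some respondents, plus the branch edit. Relabelling costs a sentence.
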